# Study Intervention

## Administration and/or Delivery of Study Intervention

**Usual smoking cessation care at TWUHC, RFPC, and PHP**. Patient participants will be required agree to attend usual smoking cessation care that is available to all clinic patients who receive clinical services at the clinic. Usual cessation care includes weekly one-on-one counseling by on-site behavioral counselors and pharmacist-dispensed NRT (i.e., transdermal patch, the gum or lozenge, the primary cessation medications in this clinical trial) covered by health insurance for at least 12 weeks.

| **Table 1: Escalating Contingency Management Schedule for Intervention Group^** | | | | |
| --- | --- | --- | --- | --- |
|  | Visit frequency | # of Visits | Intervention group potential earnings | |
|  |  |  | Total for time period | Average per visit |
| Week 1 | Daily | 7 ($13.00-16.00) | $101.50 | $14.50 |
| Weeks 2 – 4 | Bi-weekly | 6 ($16.50-19.00) | $106.50 | $17.75 |
| Weeks 5 – 13 | Weekly | 9 ($19.50-23.50) | $193.50 | $21.50 |
| Weeks 14– 24 | Monthly | 3 ($24.00-25.00) | $73.50 | $24.50 |
| Total (6 months) |  | **25** | **$ 475** |  |
| ^ Incentive payment begins @ $13.00 and increases by $0.50 for each consecutively negative CO sample (<5 ppm) to a maximum of $24.50 for the last sample. | | | | |

**Intervention.** In addition to receiving usual cessation care, CM intervention participants with CO-verified abstinence will obtain a CM incentive payment, via gift cards redeemable in national retail chains, according to a pre-defined schedule. Gift card amounts and assessment frequencies are based on prior studies among individuals experiencing homelessness or with substance use disorders,^26,30,32,33,38^ and are expected to be effective in promoting smoking cessation. We think this CM schedule is close to what will be adopted; however, our results from Aim 1 will inform the protocol. Gift card amounts will begin at US $13 and increase by $0.50 for each negative CO specimen throughout the first 6 months of the program to a maximum of $24.50 per specimen for a total of 25 specimens collected through week 24 (Table 3). An escalating schedule that increases per visit incentive payment over time is especially important in this study to maintain motivation as visit frequency decreases over time. The total amount that participants can earn under the contingent incentive program through week 24 is $620, an amount comparable to what has been used in prior studies.^30-33^ Test results indicative of smoking (i.e. CO >5ppm) or missed visits will lead to resetting the gift card amount back to the initial low value, but two consecutive negative tests will restore the value back to the highest level previously achieved. ^26,30,32,33,100^

**Control condition.** Control group participants will receive a fixed amount of $5 for attending each abstinence assessment visit and participate in usual cessation care, as described above.^32^ This approach has been used in a prior study of CM for smoking cessation among homeless adults.^32^

**Abstinence assessment schedule*.*** All other aspects of the study protocol will be identical across the two experimental groups. Participants will be asked to choose a quit date within 7 days of providing consent,^26,30,32,33,100^ and will meet study staff at TWUHC or ZSFG on the day of the quit attempt (Table 1). Participants will meet daily for the first 7 days (week 1), twice weekly for the next 3 weeks (1 month), once weekly for the next 9 weeks (3 months), and monthly until the one-year follow-up (1 year). Assessment visit schedule is identical for both groups. At each of the scheduled assessment visits, participants will provide a CO sample and complete a short questionnaire on cigarette consumption, quit attempts since the last visit, the length of the last quit attempt, and use of medications and services. Questionnaires will be built on REDCap, and administered by study staff using an iPad.

***Abstinence assessment.*** As in prior studies, ^26,30,32,33,100^to determine eligibility for CM, we will assess point-prevalence abstinence with CO monitoring, using a cut-off of CO≤ 5 parts per million (ppm).^98^ For primary outcome assessment, we will confirm abstinence among participants who self-report abstinence and meet criteria for abstinence based on CO with urinary anatabine and anabasine (i.e. metabolites of tobacco) using a cut-off of <2 ng/ml ^101^ (analyzed by the UCSF Cancer Center Tobacco Biomarkers Core ^102^). Urinary anatabine and anabasine are tobacco alkaloids that are useful as confirmatory biomarkers to verify abstinence among patients who are using NRT for smoking cessation, and for whom urinary cotinine would not be appropriate.^101^

**Data collection reimbursements*.*** We will reimburse all participants with $20 for completing the baseline questionnaire, $15 each for questionnaires at 2, weeks, 1 month, and 3 months, and $25 each for questionnaires at 6 months and 1-year follow-up. Between 6 and 12 months, all participants will receive $5 for checking in at each monthly visit and providing a CO specimen. The total amount that all participants could earn for 1 year of participation exclusive of CM is $145 and as much as $620 inclusive of CM ($145+$475).

**Clinical outcomes for the future full-scale RCT*.*** The primary outcome for the subsequent full-scale RCT will be biochemically-verified 7-day point prevalence abstinence at 6 months. Biochemically-verified 7-day point prevalence abstinence is defined as participants (1) reporting not smoking a single cigarette in the past seven days, not even a puff; (2) having CO levels ≤5 ppm, and (3) anatabine/anabasine assays <2 ng/ml. Secondary outcomes include 7-day point prevalence abstinence at 2 weeks and 3 months, and prolonged abstinence at each follow-up visit as per recent guidelines.^122^ We will also assess total number of CO-negative samples, longest duration of abstinence (i.e., total number of un-interrupted days of abstinence), total number of visits attended, and cigarette consumption for those unable to quit between the treatment groups. We will evaluate abstinence at 1 year to assess this outcome 6 months after incentives stop. In this pilot, we will assess the feasibility and acceptability of collecting each of these outcomes.

## Adherence Assessment

Using a combination of qualitative and quantitative methods, we will evaluate whether: 1) we met our screening and recruitment goals, 2) the randomization scheme worked and that participants were willing to be randomized, 3) the CM intervention was delivered with fidelity, 4) the retention procedures enabled tracking and retention, 5) the outcome assessments were valid, reliable, and complete, and 6) participants adhered to the protocol (Table 2).

| **Table 2: Feasibility and acceptability outcomes** | | |
| --- | --- | --- |
| Outcomes | **Measure** | **Threshold** |
| Screening | # opting out, # screened | 40 screened per month |
| Recruitment | # enrolled per month | 8/month for 12 months |
| Randomization | Proportion enrolled who are randomized | 90% randomized to intervention and control arms^32^ |
| Fidelity | Observations of incentive payment delivery | Incentive payments that are due are delivered within 2 days of the visit by study staff |
| Adherence | Protocol adherence to the CO assessment schedule  Attendance to counseling sessions  Adherence to NRT among those prescribed NRT | 75% of those enrolled will provide a CO sample at 60%-70%, i.e., 14 -17 out of 25 possible assessment visits^32,33^  75% will attend at least 6 out of 12 counseling sessions during the treatment duration^33^  75% will adhere to using NRT for at least half of the treatment duration^33^ |
| Retention | Proportion of the sample retained as a result of retention procedures | 2 weeks (85%), 3-month (85%), 6-month (75%), and 1 year (75%) retention rates |
| Assessment | Proportion who completed all questionnaires | 75% completed all questionnaires |
| Acceptability | Questionnaire and qualitative interviews with staff and patients | 75% satisfied with the overall intervention |

Our threshold estimates for outcomes are based on findings from prior studies. For example, for the outcome of adherence to the CO assessment visits, a prior study showed that 78% of participants attended half of the assessment visits. Another study showed that participants provided a CO reading on average for 60% of the total possible assessment visits.^32,33^ We will assess the following process outcomes: number of counseling sessions attended (verified through the EHR), prescribed NRT (verified through the EHR), use of NRT and number of days used (determined by self-report at each assessment visit), total number of follow-up visits, number and amount of incentives received, and the incentive cost per quit attempt (i.e., the cost of incentives for a participant who achieves abstinence at each time point compared to a participant who does not). We will explore perceptions around CM payment amounts and perceived efficacy of the payment amounts in motivating long-term abstinence. We will conduct this evaluation using a combination of methods including notes/memos from staff during the study and in-depth interviews with clinic staff and patients at the TWUHC, RFPC, and PHP around satisfaction with the clinical trial. We will invite patient (n=15) and staff (n=8) participants to participate in a closing interview about the study.

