## Statistical Analysis Plans

1. ***Statistical analyses****.* Because pilot studies are too small to definitively test hypotheses or estimate precise effect sizes, we do not propose any inferential statistics. Primary analyses will include descriptive statistics of the feasibility and acceptability indicators, comparing each statistic (e.g., % retained) to its tabled threshold (above, see Section 5.2). Above-threshold findings will suggest a reasonable level of feasibility and acceptability for the corresponding aspects of study procedures. Any sub-threshold finding would suggest that remedial modifications to study procedures and/or design would be required prior to moving forward with a full-scale RCT. We also will examine descriptive statistics of the primary and secondary clinical outcomes and include exploratory analyses of relevant biological variables such as age, sex, and race/ethnicity. To the extent possible, descriptive anaylses will consider whether feasibility and acceptability outcomes were consistent across service providers and service settings.

.

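### Item 5 of the feasibility evaluation promises validity, reliability and completeness of outcome assessment, but the protocol measures only completeness

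*Protocol*

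**What the plan says.** Section 5.4 lists six feasibility questions and refers to Table 2 for how they will be judged. The fifth is whether "the outcome assessments were valid, reliable, and complete". The corresponding Table 2 row, Assessment, gives the measure "Proportion who completed all questionnaires" and the threshold "75% completed all questionnaires".

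The nearest other row is Adherence, whose CO criterion reads "75% of those enrolled will provide a CO sample at 60%-70%, i.e., 14 -17 out of 25 possible assessment visits".

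Section 9.3 (Statistical Analysis Plans) makes the primary analysis descriptive, "comparing each statistic (e.g., % retained) to its tabled threshold". It explains a pass as follows: "Above-threshold findings will suggest a reasonable level of feasibility and acceptability for the corresponding aspects of study procedures".

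On data collection, section 5.1 says that at each scheduled assessment visit "participants will provide a CO sample and complete a short questionnaire on cigarette consumption". For the primary outcome, "we will confirm abstinence among participants who self-report abstinence and meet criteria for abstinence based on CO with urinary anatabine and anabasine". Section 6.2.2 (Visits 24-26) has the urine collected at 6 months from those who report abstinence and have a CO reading below 5 ppm.

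**The concern.** The evaluation question names three properties, and the measure attached to it addresses one of them, for questionnaires only. A participant can complete every questionnaire and report abstinence that CO or the assay contradicts. The row's result cannot show how often that happens.

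The gap matters most for the outcomes that rest on self-report plus CO without the assay. In section 2.2 these are 7-day abstinence at 3 and at 12 months, and prolonged abstinence at 3 and 6 months. How far they can be trusted depends partly on how often the assay overturns self-report plus CO at 6 months, the one time point where all three are available. Intervention participants are paid on their CO result, while controls receive a fixed $5 for attending. Agreement could therefore differ by arm; that is a possibility to look at, not something the protocol establishes.

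The pilot exists to decide which procedures carry into a full-scale trial, and it already collects the data needed to look at this.

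**Working it through.** **1. Match each promised property to a measure.** The search covered every row of Table 2, the process outcomes listed after it, the objectives tables (sections 2.1 and 2.2), and sections 9.3 and 9.3.2.

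| Property in item 5 | Measure found |
| --- | --- |
| Complete | Questionnaire completion (Assessment row); CO samples provided (Adherence row) |
| Valid | None. Biomarkers enter the abstinence definition, but no agreement or discordance statistic is named |
| Reliable | None. No repeatability statistic is named |

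The process outcomes concern counselling, NRT, visits and incentives. The interviews concern satisfaction and views of the payments. Section 9.3.2 speaks of the feasibility of collecting outcome data. None of these fills the two empty rows.

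**2. What decides the Assessment row.** Inputs: N = 90 (section 3.2) and a threshold of 75% (Table 2).

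- Pass mark: 0.75 × 90 = 67.5, so 68 participants, taking all 90 as the denominator.
- Chance of passing: P(X ≥ 68) with X ~ Binomial(90, p), where p is the true completion rate. This gives 0.15 at p = 0.70, 0.51 at 0.75, 0.88 at 0.80 and 0.99 at 0.85.

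Only p enters. Agreement between self-report, CO and assay appears nowhere in the rule, so the result is the same at any level of discordance.

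**3. Visit data available for self-report against CO.** Table 1 has 25 visits up to 6 months, so at most 25 × 90 = 2,250 paired records. The Adherence criterion does not imply 60% to 70% of that total, because it applies to 75% of participants and not to the average. At the lowest passing result, 68 participants × 14 visits = 952 readings, with the other 22 participants unspecified. An agreement measure would use only the records with self-reported abstinence, a number the protocol does not give.

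**4. Assay samples available at 6 months.** The protocol gives no expected abstinence rate, so this step rests on assumptions: 68 retained (75% of 90, rounded up) and 10%, 20% or 30% of them negative on self-report and CO.

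- Samples: 68 × 0.10 = 6.8, 68 × 0.20 = 13.6, 68 × 0.30 = 20.4, so about 7, 14 and 20.
- Exact (Clopper-Pearson) 95% limits for x confirmed of n: the lower is the 0.025 quantile of Beta(x, n − x + 1), the upper the 0.975 quantile of Beta(x + 1, n − x).
- With roughly 80% confirmed: 6/7 gives 0.42 to 1.00, 11/14 gives 0.49 to 0.95, and 16/20 gives 0.56 to 0.94.
- If every sample is confirmed, 7/7 still has a lower limit of 0.59, and 20/20 one of 0.83.

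Split evenly by arm, this is roughly 3 or 4 (7/2) to 10 (20/2) samples per arm.

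**5. Who gets the assay.** Sections 2.1 and 5.1 define CO abstinence as 5 ppm or less. Section 6.2.2 triggers urine below 5 ppm. Read literally, a self-reported abstainer at exactly 5 ppm meets the CO criterion but gives no sample, so the assay denominator would be incomplete.

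**The case against.** The strongest reply is that little follows from the mismatch. Four parts of it stand.

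- **A pass does not certify validity.** A reader might infer that 75% completion would be the basis for declaring the outcome assessments valid and reliable. No section says so. Section 9.3 reads a pass only as reasonable feasibility and acceptability, and section 5.4 also mentions qualitative methods.
- **The 6-month outcome is protected.** A reader might infer that discordance inflates the primary abstinence proportion. It does not: self-report, CO and assay must all be met, so a discordant participant counts as not abstinent.
- **The full-scale verification is not waiting on this.** Section 5.1 already names self-report, CO and assay for the primary outcome of the later trial. The information bears mainly on the CO-only outcomes.
- **The assay comparison will be sparse.** Step 4 shows that it cannot settle a difference between arms. Urine is also taken only from those negative on both other measures, so it can reveal only smoking that they missed.

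It could also be said that a discordance table is normal content for a statistical analysis plan not seen here. That part does not stand. The protocol itself fixes the question, the measure, the threshold and the decision rule, and these do not match. An analysis plan that followed Table 2 would repeat the mismatch.

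**Conclusion.** The point holds in a limited form. Two of the three properties in item 5, validity and reliability, have no measure anywhere in the protocol. Completeness is covered for questionnaires and, through the Adherence row, for CO samples. The Assessment row therefore says nothing about disagreement between self-report and CO, or about how often the assay overturns both.

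No endpoint, threshold or arm comparison is made wrong by this. The loss is that the pilot would leave unreported information it already collects and which bears on its CO-only outcomes. The mismatch rests on the text alone. The pass mark assumes a denominator of 90. The 7 to 20 assay samples depend on the assumed 68 retained and 10% to 30% negative on both, and serve only to show that the estimate will be rough.

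**What to change.** In the Assessment row of Table 2, keep questionnaire completion for completeness and add two descriptive measures without a threshold:

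- (a) among visit records with self-reported abstinence and a CO reading, the percentage with CO ≤5 ppm, overall and by arm;
- (b) among participants abstinent by self-report and CO at 6 months, the number and percentage confirmed by assay, overall with an exact interval, and by arm as counts only.

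Neither would change whether the row passes; they would report what it now omits. The interval in (b) conveys precision and is not a test, so it fits the descriptive intent of section 9.3.

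Reconcile the urine trigger in section 6.2.2 (below 5 ppm) with the outcome definition (5 ppm or less), so that the denominator of (b) is complete.

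Delete reliability from item 5 unless a repeatability measure on items that truly overlap is named. The short form asks about quit attempts since the last visit, while the long one asks about ever and the past year, so those items would not serve.

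The cost is two small descriptive tables from data already planned, the second imprecise, plus the wording changes.

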## Sample Size

We expect to enroll 90 participants in the RCT, with 45 randomized to control and 45 randomized to intervention. We expect to screen 40 eligible participants per month, of which we anticipate that 10 (33% participation rate) will agree to enroll, for a goal enrollment of 8 participants per month over 12 months.

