## Randomization/Assignment to Intervention

Randomization will be stratified by recruiter and a binary nicotine dependency code determined by participant response to a single item asked during study enrollment: "How soon after you wake up do you smoke your first cigarette?" (≤30 minutes coded as 'high' dependency; >30 minutes coded as 'low' dependency; Fagerström 2003). Before initiating the study, stratum-specific sequential ID numbers will be randomly pre-assigned to experimental groups in blocks of random size. The PI will be blinded to this assignment, and only the study’s statistician ([name]) will have access to the linkage between ID numbers and intervention assignments. The study ID numbers and corresponding experimental group assignments will be preloaded into REDCap. When a participant is enrolled, REDCap will assign the first available ID number within the appropriate stratum. After completing the baseline interview, participants will be informed of their study ID number and their experimental group assignment. The study will randomize 45 participants to the intervention arm and 45 to the control arm (n=90).

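### The Randomization criterion in Table 2 (90% of those enrolled are randomized) does not test whether participants were willing to be randomized

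*Protocol*

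**What the plan says.** The Adherence Assessment section (5.4) lists six questions for the pilot. The second is whether "the randomization scheme worked and that participants were willing to be randomized". The matching row of Table 2 has the measure "Proportion enrolled who are randomized" and the threshold "90% randomized to intervention and control arms", referenced to a prior trial.

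Section 4.6 describes the mechanism. Before the study starts, "stratum-specific sequential ID numbers will be randomly pre-assigned to experimental groups in blocks of random size". Then: "When a participant is enrolled, REDCap will assign the first available ID number within the appropriate stratum". Disclosure follows: "After completing the baseline interview, participants will be informed of their study ID number and their experimental group assignment".

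Section 3.2 gives the counts: "We expect to enroll 90 participants in the RCT, with 45 randomized to control and 45 randomized to intervention". Section 4.6 repeats the total of 90.

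Section 6.2.1 lists the screening activities that follow informed consent. Eligibility review comes first and randomization last. No section defines *enrolled* separately from consented or randomized.

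Section 9.3 makes the comparison of each indicator with its tabled threshold the primary analysis. A result above threshold is read as reasonable feasibility. A result below it calls for changes before a full-scale trial.

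**The concern.** A progression criterion is useful only if it can fail when the thing it stands for goes wrong. Here a person who objects to random assignment can show it in two ways. They can decline before enrolment, in which case they never enter the denominator. Or they can leave after hearing their arm, in which case they already count in the numerator. The row registers neither.

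Reaction to allocation is a plausible problem in this design. Participants know their arm. Section 5.1 gives controls a flat $5 per assessment visit, while Table 1 offers the intervention arm contingent payments totalling $475. If the row passes automatically, the Section 9.3 rule will report this aspect of the design as feasible without evidence on willingness, and the full-scale trial would inherit that reassurance.

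**Working it through.** The protocol gives no sample-size or power figure to reproduce, and the 90% threshold is cited rather than derived. The check is what values the ratio can take under each reading of *enrolled*, and what the other Table 2 rows would pick up.

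**Inputs**
- Planned enrolled: 90 (Section 3.2). Planned randomized: 45 + 45 = 90 (Sections 3.2 and 4.6).
- Threshold: 90% (Table 2), that is 0.90 × 90 = 81 of 90.
- Recruitment threshold: 8 per month for 12 months = 96 (Table 2).
- Two-week retention threshold: 85%, pooled over arms (Table 2).

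**Reading A: enrolment triggers assignment (Sections 3.2 and 4.6)**

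Ratio = randomized / enrolled = 90/90 = 100%, against 90%. The result does not depend on willingness.

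For comparison, suppose the measure were free to vary with n = 90. Passing would need at least 81, and the binomial probability of passing would be:

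| True rate | P(at least 81 of 90) |
| --- | --- |
| 95% | 0.986 |
| 90% | 0.588 |
| 85% | 0.115 |
| 80% | 0.009 |

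Under Reading A it is 1.000 throughout.

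**Reading B: enrolled means consented (assumption, suggested by the order in Section 6.2.1)**

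Hold the number randomized at 90 and vary the number consented:

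| Consented | Ratio | Against 90% |
| --- | --- | --- |
| 96 | 93.8% | passes |
| 100 | 90.0% | passes |
| 101 | 89.1% | fails |
| 105 | 85.7% | fails |

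The row can now fail. But eligibility review, including the CO check, falls between consent and randomization. The missing people are an unknown mix of those found ineligible and those who withdrew, so a shortfall cannot be read as unwillingness.

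**What the Retention row would pick up**

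Suppose k controls leave on learning their arm and nobody else is lost. Pooled retention = (90 − k)/90.
- k = 15 (33% of controls): 75/90 = 83.3%, below 85%, flagged.
- k = 14 (31%): 76/90 = 84.4%, flagged.
- k = 13 (29%): 77/90 = 85.6%, passes.

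Up to 13 of 45 controls could therefore leave with both the Randomization and two-week Retention rows passing. Any other attrition lowers that number. A flag, when it comes, does not give the reason for leaving.

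**The case against.** Four points on the other side have weight.

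*The 100% rests on an undefined word.* Enrolment is elsewhere a process: Section 4.6 takes the stratification item during it, and Section 6.2.1 starts with consent. The recruitment target of 96 against 90 randomized would give 93.8% (though 8 per month may be rounding). This stands. It is why the point is put under two readings, and neither makes the row a measure of willingness. Under Reading B the ratio is a mixed signal rather than an empty one, since some who consent may withdraw before assignment.

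*The pilot has other sources.* A reader might infer that the study cannot learn at all whether people accept randomization. The documents do not support that. Section 5.4 promises qualitative as well as quantitative methods, counts opt-outs at screening, and plans staff notes and closing interviews with 15 patients and 8 staff. These sources are limited: the opt-out count has no threshold or stated reason category, and the interviews concern satisfaction and are not said to include decliners.

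*Retention catches gross loss.* Losing 15 of 45 controls would breach the 85% threshold, so it would be wrong to say that large differential loss passes unseen. Losses somewhat smaller can pass, as shown in the working.

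*The row may be an operational check.* The question in Section 5.4 has two parts, and the ratio can serve the part about whether the scheme worked. That is a fair use of it. The willingness part is then left with no quantitative measure.

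A reader might also see a contradiction between 90% of 90 = 81 and the planned 90 randomized. There is none: 90% is a minimum to pass, not a forecast.

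**Conclusion.** The concern holds for the quantitative criterion. As written, the Randomization row is uninformative about willingness to be randomized. It is about 100% by procedure if enrolment triggers assignment, as Sections 3.2 and 4.6 have it. It is confounded with ineligibility if *enrolled* means consented. Because Section 9.3 makes the threshold comparison the primary analysis, following the plan would give a falsely reassuring answer to one of its stated questions.

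The size is one of the feasibility indicators, with no direct effect on participants and none on the clinical outcomes, which are descriptive. The retention illustration assumes that all loss is among controls. The Reading B figures assume 90 randomized and a range of consented numbers, which the protocol does not give. The measure and threshold are fixed in the protocol itself, so this is not a detail left to an analysis plan. It should be corrected, at low cost.

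**What to change.** 1. Define *enrolled* in the protocol, in relation to consent, confirmed eligibility and ID assignment.
2. Measure willingness among people confirmed eligible before any ID is assigned, as the proportion who do not decline because of random assignment. Add a reason code to the opt-out count already planned in Table 2.
3. Report descriptively, by arm, attendance at the first (quit-day) visit and two-week retention after the arm is disclosed.
4. Keep the existing ratio only as an operational check that the assignment system worked.

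The 90% should not be carried over to quit-day attendance in each arm. It was cited for a different measure, and 0.90 × 45 = 40.5 means 41 of 45 in each arm. At a true attendance of 90%, one arm passes with probability 0.53, and both with 0.53² ≈ 0.28 (binomial, independent arms). Attendance also reflects readiness to quit and unstable housing, so it is an imperfect sign of acceptance. The sponsor should justify any threshold set for the new measures.

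The cost is a wording change in Table 2 and one code on the screening log, since visit attendance is already recorded. The reported result will be less favourable than an automatic 100%.
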